##### Variables and outcome measures

The variables presented in this section were selected to estimate the effects based on the study objectives and the logic model of the intervention. The variables that will be collected according to the measurement schedule are enumerated in Table 3.

Sociodemographic characteristics include gender, age, education, revenue, marital status, and occupation. Health status includes physical functioning, role limitations because of physical health problems, bodily pain, general health perceptions, vitality (energy/fatigue), social functioning, role limitations because of emotional problems, and general mental health (psychological distress and psychological well-being). These dimensions will be investigated using the SF-12 that is a multipurpose short-form (SF) generic measure of health status. The SF-12 Health Survey includes 12 questions from the SF-36 [66].

Level of perceived disease-management self-efficacy will be evaluated using the 6-item Self-Efficacy for Managing Chronic Disease (SEM-CD) (Stanford Patient Education Research Centre 2007) [67]. Each item consists of a question asking how confident the subject feels in different aspects of disease self-management. The observed range is from 1 to 10, with a higher number indicating a greater level of perceived disease-management self-efficacy. The score for each item is summed and then averaged to yield the mean self-efficacy score. This self-efficacy score has been shown to be responsive to change following intervention in chronic disease self-management [68].

The Health Education Impact Questionnaire (HeiQ) provides a broad profile of the potential impacts of patient education interventions [69]. HeiQ evaluates health education (imparting skills) impact as well as larger psychosocial (empowerment) impact.

The Kessler psychological distress scale K-6 is a measure of nonspecific psychological distress that is sensitive to discriminating community DSM-IV cases from non-cases in the general population [70,71]. K-6 is a score derived from the sum of the scores of the responses to each of the six questions on mental illness.

The Disease Burden Morbidity Assessment (DBMA) and a questionnaire on health behaviours (eating habits, physical activity, smoking and alcohol consumption) will be used to characterize patients in different groups. Moreover, referral diagnoses, comorbidities and selected interventions will be evaluated in each group.

##### Data analysis

We will first describe participants’ characteristics in each group, using means and standard deviations for continuous variables, and percentages for categorical variables. The *t*-test (for continuous variables) and the chi-square test (for categorical variables) will be used to compare baseline characteristics across study groups.

To evaluate short-term effects, Groups A and B will be compared on T2 scores (continuous variables such as self-efficacy, health education impact) with an analysis of covariance (ANCOVA) adjusted for T1 scores [72]. If the groups differ at baseline despite randomization, the ANCOVA will also be adjusted for the relevant variables [73]. The independent variable “Group” will be tested for significance at the 5% level.

To document effects over a year, a repeated measures analysis of variance will be used to study the evolution of continuous variables collected three times in Group A [74]. Mid-term effects will be evaluated by comparing T3 measurements in Group A (modifiable risk factors, functional health status and psychological well-being) with the same variables measured in Group C (from the PRECISE cohort) using an ANCOVA adjusted for T1 scores and non-equivalent baseline characteristics (variables not used for matching) [73]. Since groups A and C will be matched on four variables only, they will be considered independently in the analysis. Again, the variable “Group” will be tested for significance at the 5% level.

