**Methods/Design:**

The implementation of the intervention will be evaluated using descriptive qualitative methods to collect data from various stakeholders (decision-makers, primary care professionals, CDPM professionals and patients) before, during and after the implementation. The evaluation of the effects will be based on a combination of experimental designs: a randomized trial using a delayed intervention arm (n = 326), a before-and-after design with repeated measures (n = 163), and a quasi-experimental design using a comparative cohort (n = 326). This evaluation will utilize self-report questionnaires measuring self-efficacy, empowerment, comorbidity, health behaviour, functional health status, quality of life, psychological well-being, patient characteristics and co-interventions. The study will take place in eight primary care practices of the Saguenay region of Quebec (Canada). To be included, patients will have to be referred by their primary care provider and present at least one of the following conditions (or their risk factors): diabetes, cardiovascular diseases, chronic obstructive pulmonary disease, asthma. Patients presenting serious cognitive problems will be excluded.

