Since it is possible that participants in different groups and phases might come in contact with each other as many will be recruited in the same practice, some precautions will be taken in order to minimize the before and after evaluation biases. To prevent selection bias, the rigorous randomization methodology and allocation concealment process described previously will be respected throughout the project. The methods were reviewed and approved by the Research Ethics Board of the CSSSC and the measurement tools were validated. We expect a response rate greater than 80% and baseline measurements will be comparable in the sense that no significant differences will exist between the groups with respect to age, gender and pre-test measurements. If necessary, the statistical models will be adjusted to ensure comparability of the groups. Each subject intervention will last less than three months and the clinical intervention period is limited to 12 months in order to ensure a contemporaneous data collection.

As stated in the logic model, with the three-month delay design we seek to examine: (1) whether the immediate intervention group (Group A) will have changes at 3 months that are sustained; (2) whether there will be changes in the first 3 months before the intervention with Group B; (3) whether the short-term results of Group A will be different from those of Group B; and (4) whether the outcomes of Group A can be sustained one year later. Theoretically, it is anticipated that these short-term results in attitudes and behaviors of patients will be the precursors of the mid-term changes expected in the maintenance of a healthy lifestyle, quality of life and psychological well-being.

In each clinic where the intervention will be deployed, patients eligible to receive the intervention must be between 18 and 75 years of age and present at least one of the following conditions: diabetes, cardiovascular disease, chronic obstructive pulmonary disease (COPD), asthma or risk factors (smoking, obesity, dyslipidemia, glucose intolerance, and metabolic syndrome). Patients with serious cognitive problems will be excluded.

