**Other variables**	
Participant characteristics	Sex, age, socioeconomic status, education, referral diagnosis
Co-intervention	Questionnaire on co-interventions

To document the effect over a year (mid-term), a repeated measures design is proposed. Thus, all patients in Group A will be reassessed a third time (T3), one year after T1. The T3 questionnaire will be identical to the one used at T1 and T2 (Figure 2).

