##### Sample size and statistical power

The required sample size for the randomized clinical trial was calculated for the two main variables (measured with the SEM-CD and the heiQ) with a two-sided α = 0.05 and 80% power. First, for continuous scores, 64 participants in each group will allow to detect a medium effect size (ES=0.5) [75]. In addition, for the heiQ, results are also expressed as the percentage of patients improving at least half a standard deviation. In a before–after study, 35% of patients receiving the intervention presented an improvement of this magnitude [69]. Using these data in a conservative scenario providing for improvement in 20% of control participants, 138 patients are required in each group to detect a 15% difference. Accounting for an anticipated drop-out rate of 15%, 326 patients will be randomized, 163 in each group. A smaller ES of 0.34 will thus be detectable for continuous scores.

Comparison of the 138 subjects in Group A, re-measured at T3 to the same number of subjects selected in the PRECISE cohort, will also allow detection of an ES of 0.34 when measuring mid-term effects (α = 0.05, power = 80%). An additional 15% will also be enrolled in anticipation of withdrawals.

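### The repeated-measures ANOVA planned for Group A's one-year course ordinarily drops patients without T3; a mixed model would keep their earlier data at almost no cost

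*Protocol article*

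**What the plan says.** The Data analysis section under Evaluation of effects (objective 2) fixes the method: "a repeated measures analysis of variance will be used to study the evolution of continuous variables collected three times in Group A". The text after Table 3 gives the intended population: "all patients in Group A will be reassessed a third time (T3), one year after T1". It adds that the T3 questionnaire is the same as at T1 and T2. One of the questions listed for the delayed design is "4) whether the outcomes of Group A can be sustained one year later".

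The abstract labels this component "a before-and-after design with repeated measures (n = 163"). The Sample size section explains that number: "138 patients are required in each group to detect a 15% difference", and then "Accounting for an anticipated drop-out rate of 15%, 326 patients will be randomized, 163 in each group". For the mid-term comparison it speaks of "Comparison of the 138 subjects in Group A, re-measured at T3 to the same number of subjects selected in the PRECISE cohort".

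Table 3 lists self-efficacy and empowerment as short-term measures, taken at T1 and T2 in Groups A and B. The outcomes compared between Groups A and C at T3 are health behaviour, SF-12, K-6 and comorbidity.

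**The concern.** Classical repeated-measures ANOVA needs a full row of three scores per patient. Someone who answers at T1 and T2 and then withdraws contributes nothing, although the T2 score shows how that patient responded. The article itself expects withdrawals. The intervention is unblinded and the outcomes are self-reported, so it is plausible that the decision to return a questionnaire depends on perceived benefit.

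If it does, the completers' trajectory is not that of Group A. No control arm in this analysis would share the distortion. For self-efficacy and empowerment, the two variables on which the trial was sized, no other planned analysis reaches one year: Group B is the comparator only at T2, and Table 3 does not list these two measures for the comparison with Group C.

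**Working it through.** **1. The plan's own numbers.** Inputs from the Sample size section: 35% against 20% improving, two-sided alpha 0.05, power 80%, drop-out 15%.

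- Per group: [1.960 × √(2 × 0.275 × 0.725) + 0.842 × √(0.35 × 0.65 + 0.20 × 0.80)]² / 0.15² = 137.9, so 138. Reproduced.
- 138 / 0.85 = 162.4, so 163 per group. Reproduced.
- Detectable effect size with 138 per group: √(2/138) × (1.960 + 0.842) = 0.337, stated as 0.34. Reproduced.

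So 163 is the number enrolled in Group A and 138 the number planned for at T3.

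**2. What complete-case analysis removes.** 163 − 138 = 25 patients. The within-person change detectable with 80% power, in SDs of the change, goes from 0.22 (n = 163) to 0.24 (n = 138). The cost in precision is small.

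**3. Size of a possible bias, in general.** Upward shift of the completers' mean change = share lost × (mean change in completers − mean change in leavers). At 15% loss:

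- gap 0.2 SD: 0.15 × 0.2 = 0.03 SD
- gap 0.5 SD: 0.15 × 0.5 = 0.075 SD
- gap 1.0 SD: 0.15 × 1.0 = 0.15 SD
- no gap: 0

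The documents do not give the gap.

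**4. Size under a stated dropout model.** All inputs here except the 15% are assumptions: unit SD at each visit; correlations 0.6 (T1-T2), 0.5 (T1-T3) and 0.65 (T2-T3); true change 0.34 SD at T2 and 0.20 SD at T3, so a true T3-T2 of −0.14. All the loss falls after T2, with log-odds falling by 0.25, 0.5 or 1 per SD of T2-T1 change. Simulated means:

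| Log-odds slope | Completers T2-T1 (true 0.34) | Completers T3-T1 (true 0.20) | Completers T3-T2 (true −0.14) |
|---|---|---|---|
| 0 (random) | 0.34 | 0.20 | −0.14 |
| −0.25 | 0.37 | 0.22 | −0.15 |
| −0.5 | 0.40 | 0.24 | −0.16 |
| −1 | 0.45 | 0.27 | −0.17 |

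A likelihood-type estimate using all T1 and T2 data gave 0.20 for T3-T1 in every row.

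**5. Why the table has this shape.** Selection acts on T2-T1, so the other contrasts move only through their regression on it. Cov(T2-T1, T3-T1) = 0.65 − 0.6 − 0.5 + 1 = 0.55, and Var(T2-T1) = 2 − 2 × 0.6 = 0.80, so the slope is 0.55/0.80 = 0.69. A shift of 0.06 in T2-T1 (slope −0.5) moves T3-T1 by 0.69 × 0.06 = 0.04 and T3-T2 by 0.04 − 0.06 = −0.02. Both levels rise, T2 more than T3. The share of the T2 gain retained is 0.24/0.40 = 60%, against a true 0.20/0.34 = 59%.

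**6. What these slopes imply about leavers.** Leavers' mean T2-T1 = (0.34 − 0.85 × completers' mean)/0.15:

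- slope −0.25: 0.17 SD
- slope −0.5: about 0
- slope −1: −0.28 SD

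**7. Against sampling error.** Var(T3-T1) = 2 − 2 × 0.5 = 1, so the standard error with 138 patients is 1/√138 = 0.085 SD. The shift of 0.02 to 0.07 SD is below one standard error.

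**The case against.** **Missing-data handling belongs in the SAP or full protocol.** Largely right: the article states no complete-case rule, and its silence on imputation is not a finding. The article does name the method, however, and the ordinary form of that method is complete-case. A later plan would have to work around that choice.

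**The analysis is secondary and has a controlled companion.** It is neither the randomized comparison at T2 nor the powered one-year comparison with Group C. That stands for the outcomes Table 3 assigns to Groups A and C. It does not help self-efficacy and empowerment.

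**The bias is conjecture and small.** This stands in part. Nothing in the documents shows who leaves, and the article does not say how the 15% divides between losses before and after T2. Patients lost before T2 have no T2 score for any model to use.

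A reader might infer two stronger points, and neither is supported:

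- *That the analysis falls short of a promised 163.* The abstract's figure is the enrolled number. The Sample size section allows for the loss and refers to "Comparison of the 138 subjects in Group A, re-measured at T3".
- *That selective loss would pass for maintenance of effect.* Under the dropout model above, the completers' T3-T2 decline is slightly larger than the true one (−0.15 to −0.17 against −0.14), and the share of the gain retained is almost unchanged. The inflation is in the change from baseline, at both visits.

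**Conclusion.** The point holds as a cheap improvement. The named method ordinarily sets aside about 25 of 163 Group A patients at the planned loss, some of whom may have T1 and T2 scores. If leaving after T2 depends on poor T2 response, the completers overstate change from baseline: by 0.02 to 0.07 SD at T3 and by 0.03 to 0.11 SD at T2 under the assumptions shown. With random loss there is no bias. These sizes rest on assumed correlations, true changes and dropout slopes, and on placing all the loss after T2; the documents supply only the 15%. The plan has no sample-size error here, and false maintenance between T2 and T3 is not shown.

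**What to change.** In the Data analysis section, replace the repeated-measures ANOVA for Group A with a linear mixed model for repeated measures: time (T1, T2, T3) as a factor, unstructured covariance, and every Group A patient with at least one measurement included. State the contrasts T2-T1, T3-T1 and T3-T2, and keep the completers' analysis as a sensitivity analysis.

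The cost is a change of wording, with no new patients, visits or data. The small downside is that the model still assumes that observed scores explain dropout, so loss that depends on the unseen T3 state would remain uncorrected.

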##### Sample size and statistical power

The required sample size for the randomized clinical trial was calculated for the two main variables (measured with the SEM-CD and the heiQ) with a two-sided α = 0.05 and 80% power. First, for continuous scores, 64 participants in each group will allow to detect a medium effect size (ES=0.5) [75]. In addition, for the heiQ, results are also expressed as the percentage of patients improving at least half a standard deviation. In a before–after study, 35% of patients receiving the intervention presented an improvement of this magnitude [69]. Using these data in a conservative scenario providing for improvement in 20% of control participants, 138 patients are required in each group to detect a 15% difference. Accounting for an anticipated drop-out rate of 15%, 326 patients will be randomized, 163 in each group. A smaller ES of 0.34 will thus be detectable for continuous scores.

Comparison of the 138 subjects in Group A, re-measured at T3 to the same number of subjects selected in the PRECISE cohort, will also allow detection of an ES of 0.34 when measuring mid-term effects (α = 0.05, power = 80%). An additional 15% will also be enrolled in anticipation of withdrawals.

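### Two main variables are each tested at 5% with no rule for whether one or both must succeed, and the heiQ responder comparison that sets N has no matching between-group test

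*Protocol article*

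**What the plan says.** Sample size and statistical power opens: "The required sample size for the randomized clinical trial was calculated for the two main variables (measured with the SEM-CD and the heiQ"). For both variables, the randomized comparison is planned "with a two-sided α = 0.05 and 80% power". Continuous scores need 64 per group for an effect size of 0.5. A second calculation then sets the size of the trial. It rests on the statement that "for the heiQ, results are also expressed as the percentage of patients improving at least half a standard deviation". The intervention rate of 35% comes from a before-after study of patients who received the intervention. The control rate is introduced with "Using these data in a conservative scenario providing for improvement in 20% of control participants". This leads to 138 per group, then to 163 per group and 326 in total after 15% drop-out, with a detectable effect size of 0.34 for continuous scores.

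Under Data analysis (evaluation of effects), the short-term comparison, which takes the T1 score as covariate, is described as follows: "Groups A and B will be compared on T2 scores (continuous variables such as self-efficacy, health education impact) with an analysis of covariance (ANCOVA"). Then: "The independent variable “Group” will be tested for significance at the 5% level". The only test named for categorical variables concerns baseline: "the chi-square test (for categorical variables) will be used to compare baseline characteristics across study groups".

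**The concern.** Two variables share main status, and each is tested at the full 5%. A reader cannot tell whether the trial succeeds on one significant result or needs two. The first reading raises the chance of a false claim above 5%. The second lowers the chance of success below 80% at the planned effects. The choice would otherwise be made with the results in view.

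The second difficulty is that the sizing section and the analysis section refer to different endpoints. The responder proportion more than doubles the required size, from 64 to 138 per group, yet no between-group test of that proportion is described. The 80% power attached to it therefore belongs to no stated analysis. It also depends on a control rate for which the cited study, having treated patients only, can give no estimate.

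**Working it through.** **1. The plan's own figures reproduce.**
- Responders, 35% versus 20%, pooled-variance formula, mean proportion 0.275: n = [1.960·√(2·0.275·0.725) + 0.842·√(0.35·0.65 + 0.20·0.80)]² / 0.15² = 137.9, so 138 per group.
- Drop-out: 138 / 0.85 = 162.4, so 163 per group and 326 in total.
- Continuous scores: 64 per group at effect size 0.5 has 80.1% power (noncentral t).
- Detectable effect at 138 per group: (1.960 + 0.842)·√(2/138) = 0.337, reported as 0.34.

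**2. Trial-level error and power.** The correlation between the two test statistics is not given, so a range is shown. Independence gives 1 − 0.95² = 9.75% and 0.80² = 64%. The other rows use the bivariate normal distribution.

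| Correlation | Error if either suffices | Power if both are required (80% each) |
|---|---|---|
| 0 | 9.75% | 64% |
| 0.5 | 9.1% | 69% |
| 0.9 | 7.0% | 75% |

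The power column applies at effects where each test has exactly 80%. At effect size 0.5 and 138 per group, each test has 98.6%, and joint power under independence is 0.986² = 97%. Adding the responder comparison as a third independent 5% test would give 1 − 0.95³ = 14.3%. Its overlap with the continuous heiQ score would make the true figure lower.

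**3. Endpoint that sets N versus endpoint analysed.** Sample size section: N is set by the heiQ responder proportion. Data analysis section: A versus B is compared by ANCOVA on continuous T2 scores, and chi-square is assigned to baseline characteristics. The two sections do not meet.

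**4. Sensitivity to the control rate.** Power = Φ{[Δ√n − 1.960·√(2·p̄·q̄)] / √(p₁q₁ + p₂q₂)}, with n = 138 and the intervention rate held at 35%.

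| Control rate | Power |
|---|---|
| 15% | 97% |
| 20% | 80% |
| 22% | 67% |
| 25% | 44% |
| 30% | 14% |

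Whether 20% is cautious depends on how stable the score is. Assume normal scores, no mean change in controls and test-retest correlation r (none of this is in the article). The share of controls gaining half an SD by chance is then 1 − Φ(0.5/√(2(1 − r))): 13% at r = 0.9, 21% at 0.8, 26% at 0.7 and 31% at 0.5. A rate of 20% corresponds to r of about 0.82.

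**5. Power with error controlled.** At alpha 0.025 with 138 per group, the detectable effect is (2.241 + 0.842)·√(2/138) = 0.371. If the T1–T2 correlation is 0.5 (assumption), ANCOVA multiplies this by √(1 − 0.25) = 0.866, giving 0.32.

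**The case against.** The strongest reply is that the article states 5% and 80% per variable, and that every one of those figures is right. It never claims a family-wise error or a joint power. Testing each variable at 5% is also compatible with requiring both, or with a fixed testing order, and neither of those needs a split of alpha. A multiplicity rule and a responder test could sit in a full protocol or SAP that is not shown. This stands to the extent that the per-test figures need no correction and that the 7.0% to 9.75% range applies only under an either-suffices rule, which the article does not state. It does not remove the point, because the article does not defer the matter: it fixes the level and the test for both variables and leaves the decision rule open.

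A reader might infer that 20% is too low and the claim of conservatism false. The documents do not support that. They give no control rate and no test-retest correlation, and at r = 0.9 chance alone would produce only 13%, so 20% would be cautious. What can be said is that 20% has no stated source.

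A reader might also infer that the trial is underpowered. That does not follow either. The missing responder test takes nothing from the planned ANCOVA, which at 138 per group has about 80% power at effect size 0.34 and 98.6% at 0.5, before any gain from T1 adjustment.

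**Conclusion.** The point holds at trial level. As written, the plan gives either a family-wise error of 7.0% to 9.75% or a joint power of 64% to 75%, depending on a success rule that is not stated. The ranges cover correlations from 0.9 to 0 between the two tests, and the power range assumes effects that give 80% for each. Independently of any assumption, the comparison that sets N has no matching between-group test in the analysis section. The 20% control rate is unsupported rather than shown to be wrong, but modest departures matter: with 35% in the intervention arm, responder power falls from 80% to 44% if the control rate is 25%. The sample size itself does not need to change. The statements about error, endpoint and power should be brought into line.

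**What to change.** - In Data analysis, name two confirmatory tests for A versus B: the T1-adjusted ANCOVA of the SEM-CD score and that of one heiQ score named in advance. Control the pair by Holm or Hochberg at an overall two-sided 5%. Alternatively, state that both must succeed, keep 5% for each, and report the joint power.
- Label the heiQ responder comparison as supportive and name the between-group method used for it. Give a source for the 20% control rate, or show the range of power around it.
- Restate Sample size and statistical power on the analysed endpoint: 138 per arm detects an effect size of 0.37 at alpha 0.025 without adjustment, or about 0.32 if the T1–T2 correlation is 0.5, with that correlation marked as an assumption.

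The cost is wording and a somewhat stricter threshold (0.025) for the smaller p-value, which the T1 adjustment would offset if the assumed correlation holds. N stays at 326. By contrast, keeping the responder comparison confirmatory at alpha 0.025 would need 168 per arm evaluable, hence 168 / 0.85 = 197.6, or 198 per arm and 396 in total.

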### Feasibility

After a six-month implementation phase, the study will take place over 18 months and will involve eight medical clinics. To recruit 326 patients for the study and meet the minimal time between intervention and effects in one year, patient selection will need to be done within six months. At the very conservative mean rate of two patients per week per clinic, this objective should be easily achieved. Pairing 138 patients with the PRECISE cohort with a potential pool of 2197 patients from the waiting rooms of medical practices is feasible. With regard to health care providers in clinical settings, a survey was conducted in September 2010 that showed their willingness to participate.

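### The one-year comparison takes one PRECISE control per Group A patient from an existing cohort of 2197; matching up to two or three at a variable ratio would gain precision cheaply

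*Protocol article*

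**What the plan says.** The Protocol article, Sample size and statistical power, derives 138 evaluable patients per group for the randomised comparison of Groups A and B. It then inflates this: "Accounting for an anticipated drop-out rate of 15%, 326 patients will be randomized, 163 in each group".

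For the mid-term comparison with Group C the same section carries the 138 forward to one year: "Comparison of the 138 subjects in Group A, re-measured at T3 to the same number of subjects selected in the PRECISE cohort". It states a detectable ES of 0.34 and adds: "An additional 15% will also be enrolled in anticipation of withdrawals".

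Feasibility describes the task as "Pairing 138 patients with the PRECISE cohort with a potential pool of 2197 patients". The abstract gives the enrolled total for this design: "a quasi-experimental design using a comparative cohort (n = 326"), which is 163 + 163.

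Evaluation of effects says that the cohort completed questionnaires at T1 (two weeks), T2 (3 months) and T3 (12 months), and that matching is on age, gender, diagnosis and family income. Data analysis compares A with C at T3 by ANCOVA adjusted for T1 scores and for baseline characteristics not used in matching, with the two groups handled as independent samples.

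**The concern.** One-to-one allocation is efficient when each control costs as much as each treated patient. Here it does not: Group C is drawn from a cohort followed for another purpose, and an extra control is another row of existing data. Group A is capped at the 163 randomised, so the size of Group C is the only number that can be raised without recruiting anyone. According to Table 3 and Data analysis, this is also the only comparison of the mid-term outcomes (health behaviour, SF-12, K-6) against a control group. Precision is therefore worth having, and the article gives no reason for forgoing it.

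A second matter bears on the same figure. The number 138 serves both at three months (A v B) and at one year (A v C), while the article gives one drop-out rate without saying by when it applies. The reader cannot tell whether loss between T2 and T3 has been allowed for.

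**Working it through.** **Inputs from the article.** Sample size section: "with a two-sided α = 0.05 and 80% power" for the randomised comparison, and α = 0.05 with 80% power for A v C (taken as two-sided); responder rates 35% v 20%; 15% drop-out; 138 evaluable and 163 enrolled per group. Evaluation of effects and Feasibility: cohort of 2197.

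**1. The plan's own figures.**
- Responders, pooled-variance formula: n = [1.960·√(2 × 0.275 × 0.725) + 0.842·√(0.35 × 0.65 + 0.20 × 0.80)]² / 0.15² = 137.9, so 138 per group.
- Drop-out: 138 / 0.85 = 162.4, so 163 per group and 326 in total. Conversely, 163 × 0.85 = 138.6.
- Detectable ES = (1.960 + 0.842)·√(1/nA + 1/nC). For 138 v 138 this is 2.802 × 0.1204 = 0.337, which rounds to the stated 0.34. Power at 0.34 is 80.6%.

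All three figures reproduce.

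**2. Share of the cohort used.** 138 / 2197 = 6.3%, or 163 / 2197 = 7.4% if the enrolled number is taken.

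**3. More controls per patient, 138 in Group A** (same formula with nC = k × 138):

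| Ratio | Controls | Detectable ES | Power at 0.34 |
|---|---|---|---|
| 1:1 | 138 | 0.337 | 80.6% |
| 1:2 | 276 | 0.292 | 90.3% |
| 1:3 | 414 | 0.275 | 93.3% |
| 1:4 | 552 | 0.267 | 94.7% |

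Most of the gain is reached by two or three controls. The table assumes that every patient obtains the full number of matches, so it shows the most that can be gained.

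**4. If the 15% covers loss to T2 only.** Further loss from T2 to T3 is not given, so it is varied here as an assumption, starting from 138:

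| Further loss | In A at T3 | ES, same loss in C (power at 0.34) | ES, 163 controls kept |
|---|---|---|---|
| 5% | 131 | 0.346 (78.6%) | 0.329 |
| 10% | 124 | 0.356 (76.3%) | 0.334 |
| 15% | 117 | 0.366 (73.9%) | 0.339 |
| 20% | 110 | 0.378 (71.3%) | 0.346 |

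With 117 in Group A, 1:2 matching (234 controls) gives 0.317 with 85.1% power, and 1:3 (351 controls) gives 0.299 with 89.0%.

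**The case against.** **On matching.** One-to-one matching is a legitimate choice, and the 2197 are not all usable. The cohort is undifferentiated by disease and aged 25 to 75, against 18 to 75 in the trial, and members must match on four variables. The number who qualify is not given. In a non-equivalent comparison bias is the larger threat, and a looser second or third match could trade bias for variance. This stands as a limit on the gain. It does not stand against the change if extra matches are taken only when they meet the same closeness limits as the first.

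**On drop-out.** A reader might infer that the 15% has been used up by three months, so that 80% power at 0.34 is not delivered at one year. The article does not support that conclusion. Its 15% has no time point. Read as total loss to 12 months, it gives 138 at T3, and the three-month comparison is then conservatively sized. That the rate is introduced with the randomised trial makes the other reading possible, but does not establish it. Nor must Group C shrink with Group A: the abstract's 326 implies 163 controls, the analysis is unpaired, and 117 v 163 still gives 0.339. The sentence on a further 15% does not settle the matter, because Group A cannot exceed 163; at most it enlarges Group C.

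**On the analysis.** ANCOVA on T1 scores is more efficient than the calculation, which takes no credit for it. With detectable ES scaled by √(1 − r²), a T1-T3 correlation of about 0.37 would bring 0.366 back to 0.34. The article gives no correlation, so this is an assumption, but it is a further reason not to call the 0.34 unattainable.

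**On the numbers.** The 138 and the 163 do not contradict each other: one is evaluable, the other enrolled.

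**Conclusion.** This is a cheap improvement and not an error. The stated 0.34 is correct for 138 v 138 and is not shown to be wrong at one year. Limiting Group C to one control per patient leaves precision unused: at best the detectable ES falls from 0.34 to about 0.29 at 1:2 or 0.275 at 1:3, with 138 in Group A. The real gain will be smaller if fewer cohort members qualify.

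The time point of the 15% needs one clarifying sentence. If it is loss to T2 only, the T3 figure should be restated. Under an assumed further 5-20% loss in both groups, the 1:1 detectable ES is about 0.35-0.38, with 79%-71% power at 0.34. At a further 15% loss in Group A it stays near 0.34 if all 163 controls are kept, and extra controls would more than absorb the loss.

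**What to change.** - Match each Group A patient to up to two or three PRECISE members with both T1 and T3 data, at a variable ratio. Require an exact match on gender and diagnosis and a caliper on age and family income fixed in advance, so that a second or third match is accepted only if it is as close as the first is required to be.
- Keep the planned ANCOVA. Because a variable ratio over-represents patients who are easy to match, either weight each control by one over the number matched to that patient or add the four matching variables as covariates. Weighting costs a little of the gain in step 3.
- In Sample size and statistical power, say whether the 15% is loss to three months or to 12 months, and which group the further 15% refers to. If it is loss to three months, give a separate T3 attrition assumption and the resulting detectable ES.
- Count the cohort members who meet the matching limits, then carry the resulting Group C size into the abstract and Feasibility.

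The cost is more matching work, and there may be fewer extra matches than hoped. No patients are added and no new type of model is needed.
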